## Abstract

**Background:**

The menopausal transition (MT) is a biological inevitability for all ageing women that can be associated with changes in mood, including depressive symptoms. There is tentative evidence that women who develop depression during the MT have greater risk of subsequent depressive episodes, as well as increased health morbidity and mortality. Thus, preventing depression during the MT could enhance both current and the future health and well-being of women. This study aims to test the efficacy of a client-centred health promotion intervention to decrease the 12-month incidence of clinically significant symptoms of depression among women undergoing the MT.

**Methods/Design:**

This randomised controlled trial will recruit 300 women undergoing the MT living in the Perth metropolitan area. They will be free of clinically significant symptoms of depression and of psychotic or bipolar disorders. Consenting participants will be stratified for the presence of subsyndromal symptoms of depression and then randomly assigned to the intervention or control group. The intervention will consist of eight telephone health promotion sessions that will provide training in problem solving and education about the MT, healthy ageing, depression and anxiety, and management of chronic health symptoms and problems. The primary outcome of interest is the onset of a major depressive episode according the DSM-IV-TR criteria during the 12-month follow-up or of clinically significant symptoms of depression, as established by a score of 15 or greater on the Patient Health Questionnaire (PHQ-9). Secondary outcomes of interest include changes in the severity of symptoms of depression and anxiety (Hospital Anxiety and Depression Scale, HADS), quality of life (Short Form Health Survey, SF-12), and lifestyle.

**Discussion:**

Current evidence shows that depressive symptoms and disorders are leading causes of disability worldwide, and that they are relatively common during the MT. This study will use a multifaceted health promotion intervention with the aim of preventing depression in these women. If successful, the results of this trial will have implications for the management of women undergoing the MT.

**Trial registration:**

Australian and New Zealand Clinical Trials Registry ACTRN12613000724774. Date registered: 1 July 2013.

## Background

Depression is a leading cause of disability and health-related costs in Australia and worldwide [1, 2], and affects between 4 and 14% of the population at any point in time [2]. The prevalence of depression is consistently higher in women than in men across the reproductive lifespan, with an increase in the prevalence of clinically significant depressive symptoms noted during the years that overlap with the menopausal transition (MT) [3–6]. The prospective midlife Study of Women’s Health Across the Nation (SWAN) in the United States indicated that nearly one in every four women experience clinically significant depressive symptoms at this time [7]. This, together with further confirmatory studies, led the National Institute of Aging to propose in 2010 that active screening of depressive symptoms should become an integral part of the assessment of all women going through the MT [8].

### What is the menopausal transition?

All ageing women with intact ovaries go through the MT, which is triggered by low ovarian follicular reserve that leads to elevated follicle-stimulation hormone, fluctuating oestradiol and reduced progesterone levels [9]. The MT commences at around age 47 and lasts 4 to 7 years [10]. The ‘menopause’ is the final menstrual period and occurs at a mean age of 51 years, and by age 55 nearly all women are postmenopausal [11]. Symptoms typically associated with the MT include irregular menstrual cycles, vasomotor symptoms (hot flushes and night sweats), sleep disturbances, vaginal dryness and dyspareunia, decreased libido, urinary symptoms, muscle and joint pains, and mood disturbance [10]. Importantly, typical symptoms associated with the MT (for example, hot flushes and night sweats) are amenable to change by means of biological or behavioural interventions [12, 13].

### Why is the prevalence of depressive symptoms high during the menopausal transition?

The reasons for the increased vulnerability to depression during the MT are not fully understood. Women with past history of depression are nearly five times more likely to have a recurrence of depressive illness during the menopausal transition, whereas women with no history of depression are two to four times more likely to report depressed mood compared with premenopausal women [6, 14, 15]. In some studies, the changing hormonal milieu has been associated with depressive symptoms during the MT [16, 17], but other factors may be as important, such as prolonged hot flushes, weight gain, comorbid diseases, poor social support, changing psychosocial roles, anxiety and perceived loss of control [18–21].

### Can we prevent depression during the menopausal transition?

Despite growing recognition that the MT is a period of high vulnerability to depression, no previous studies have attempted to prevent this happening. The spectrum of physiological, psychological and social changes that women undergoing the MT have to negotiate indicate that effective preventive strategies must be multifaceted (in the same way that strategies to reduce the prevalence of cardiovascular events have greater chance of success when multiple risk factors are targeted simultaneously, such as hypertension, diabetes, dyslipidaemia, physical activity, diet, alcohol use and smoking). Moreover, past history of depression increases the risk of postmenopausal depression, cardiovascular events, substance abuse and mortality [22, 23], the successful prevention and treatment of depression during the MT is expected to have long-term beneficial consequences for our ageing population. Clinical recommendations on managing the MT promote a broad approach to prevention and management of depression [24], including education, lifestyle changes (diet, exercise, smoking, and alcohol consumption), optimisation of general health and social support, minimisation of vasomotor symptoms, problem solving strategies and, if depression is prominent (that is, major depressive episode or dysthymia), antidepressant treatment and/or psychotherapy [25]. Oestrogen-containing hormone therapy is recommended for women with moderate to severe vasomotor symptoms without other contra-indications [13], and preliminary evidence suggests that it may also improve mood [16]. As the origin of depression during the MT is most likely multifactorial, its optimal management and prevention should target multiple factors, which is consistent with the results of successful interventions designed to decrease the prevalence of depression and suicide ideation in later life [26].

### Women undergoing the menopausal transition require a targeted health promotion intervention

The MT affects all ageing women with intact ovaries. Marked physiological and psychosocial changes characterise this unique period of a woman’s life, including symptoms such as hot flushes and night sweats, remodelling of body shape, shifting social roles (for example, children moving away from home), and onset of chronic illnesses (such as diabetes and hypertension). All these factors may interact to facilitate the development of depressive symptoms during the MT. As depression and poor lifestyle practices in mid life have been associated with poor health outcomes in older age [11, 27–29], developing health promotion interventions that are relevant to women in the MT seem not only desirable, but a necessity.

In summary, published observational data suggest that women undergoing the MT are at increased risk of clinically significant depressive symptoms and highlight numerous health and behavioural factors that might potentially mediate such increased risk. We have designed a health promotion intervention that seeks to address these risk factors systematically and to enhance behaviours associated with good mental health outcomes. More specifically, this study will aim to address the following:determine the efficacy of a telephone-medicated health promotion intervention, compared with usual care, in decreasing the 12-month incidence of clinically significant symptoms of depression in women undergoing the menopausal transition who do not have clinically significant symptoms of depression or mental disorders at the time of entry into the study,determine the efficacy of a telephone-mediated health promotion intervention in decreasing the 12-month incidence of major depressive episodes in women undergoing the menopausal transition, compared to usual care,measure the effect of a telephone-mediated health promotion intervention in decreasing the severity of depressive symptoms over 12 months compared to usual care,ascertain the prevalence of clinically significant symptoms of depression among community-dwelling Western Australian women undergoing the menopausal transition.

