### Participants

We will use the Australian Electoral Commission roll to obtain a random extraction of 40,000 women aged 45 to 55 years living in the Perth metropolitan area (enrolment to vote is mandatory for all adults in Australia). They will be contacted by post to confirm their perimenopausal status (menopausal transition) and to assess the prevalence of clinically significant symptoms of depression (Patient Health Questionnaire, PHQ-9 score ≥15). They will be asked to return their screening questionnaire alongside the signed consent form, and those with PHQ-9 < 15 will be invited to join the trial. This screening questionnaire will take approximately 30 minutes to complete and will collect the following information:demographics including date and place of birth, age, marital status, number of children, educational attainment, living arrangements;regularity of menstrual cycles to establish menopausal status;history of life-limiting medical illnesses;presence of significant hearing or visual impairment;current and past common medical conditions, including depressive and anxiety disorders;alcohol use, as measured by the Alcohol Use Disorders Identification Test (AUDIT, details below);history of gynaecological surgery and medical procedures (for example, contraceptive implants) that may affect the assignment of menopausal status;prescription and non-prescription medications (including hormone therapy);depressive and anxiety symptoms, as rated by the Hospital Anxiety and Depression Scale (HADS, details below);past history of schizophrenia, schizoaffective, delusional or bipolar disorder; andgeneral practitioner’s (GP) details and permission for the study team to liaise with GP.

For the trial, we will include women who are:aged 45 to 55 years;experiencing no, or sub-threshold depressive symptoms (PHQ-9 < 15);experiencing recent (last 5 years) onset of irregular menstrual cycles (≥7 days difference in length of consecutive cycles) OR ≥2 skipped cycles and at least one interval of amenorrhea of 60 or more days; andamenorrhoeic for <12 months.

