Volunteers will be excluded from participating for the following reasons:they disclose a history of gynaecological surgery that compromises the ability to assign menopausal status (that is, hysterectomy, bilateral oophorectomy, or endometrial ablation);they report an illness that may impact upon 12-month survival (for example, metastatic cancer);they receive medical treatment or undergo medical procedures that hinder ability to assign menopausal status (hormone therapy, hormonal intrauterine devices, contraceptive implants, patches or medications);there is evidence of clinically significant depressive symptoms (PHQ 9 ≥ 15) or major depressive episode at the time of assessment;there is evidence of concurrent alcohol abuse or dependency (AUDIT ≥15);they report past or current history of schizophrenia, delusional, schizoaffective or bipolar disorder;there is evidence of significant hearing impairment that may compromise telephone communication;they are not fluent in written or spoken English;they plan to leave Western Australia within the following 12 months;they report active suicidal ideation;they do not have an active GP or do not consent to the research team liaising with their GP throughout the course of the study; orthey fail to provide written informed consent.

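### Aim 4 names Western Australian women in the menopausal transition, but the design can estimate prevalence only among responding women in metropolitan Perth

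*Protocol article*

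**What the plan says.** The last of the four aims in the Background of the Protocol article is to "ascertain the prevalence of clinically significant symptoms of depression among community-dwelling Western Australian women undergoing the menopausal transition". The target is therefore state-wide.

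Under Methods/Design, Participants, the team will use the electoral roll to "obtain a random extraction of 40,000 women aged 45 to 55 years living in the Perth metropolitan area". The same sentence notes that "enrolment to vote is mandatory for all adults in Australia". The Abstract also places recruitment in Perth.

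The women are contacted by post to confirm their menopausal status and "to assess the prevalence of clinically significant symptoms of depression (Patient Health Questionnaire, PHQ-9 score ≥15"). The screening questionnaire takes about 30 minutes. On its return the section says: "They will be asked to return their screening questionnaire alongside the signed consent form". Only afterwards does selection for the trial begin: "those with PHQ-9 < 15 will be invited to join the trial".

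The Discussion presents recruitment from the roll as a way to increase external validity, and as one that lets the team approach more people if needed. Nowhere does the article restrict aim 4 to Perth or to women who reply.

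**The concern.** A prevalence estimate describes the population from which its denominator is drawn. Two steps separate the denominator here from the population that aim 4 names.

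- **Frame.** The roll extract is confined to metropolitan Perth. Women elsewhere in Western Australia have zero selection probability.
- **Response.** Among those mailed, only women who complete a long questionnaire, sign a form and post both back are counted. The questionnaire asks about mood, alcohol and psychiatric history, and seeks permission to contact the GP. Return could plausibly depend on mood, which is the quantity being estimated.

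At stake is what the trial team may conclude under aim 4. A figure from responding Perth women, presented as the Western Australian prevalence, would claim more than the data can support.

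**Working it through.** **Step 1: target against frame.** Aim 4 names Western Australia; Participants samples metropolitan Perth. If a share w of the state's women in the transition live in metropolitan Perth, then

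state prevalence = w × P(Perth) + (1 − w) × P(elsewhere).

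The design gives no information on P(elsewhere). Reading the Perth figure as the state figure makes an error of (1 − w) × [P(Perth) − P(elsewhere)]. The document gives neither w nor P(elsewhere), so this error cannot be sized. No weighting of the Perth responders can supply the missing term.

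**Step 2: sampled women against responders.** The article states no expected response rate, precision or sample size for aim 4, so there is no figure of its own to reproduce. What follows is an illustration.

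Let p be the true prevalence of PHQ-9 ≥ 15, and r the return rate of women at or above 15 relative to women below it. Then

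prevalence among responders = p × r / (p × r + 1 − p).

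Take p = 0.14, the survey figure quoted under Sample size. The values of r are assumptions.

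| r (assumed) | Calculation | Prevalence among responders | Error |
|---|---|---|---|
| 0.5 | 0.070 / 0.930 | 7.5% | −6.5 points |
| 0.75 | 0.105 / 0.965 | 10.9% | −3.1 points |
| 1 | 0.140 / 1.000 | 14.0% | 0 |
| 1.25 | 0.175 / 1.035 | 16.9% | +2.9 points |
| 1.5 | 0.210 / 1.070 | 19.6% | +5.6 points |

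For scale, the contrast quoted under Sample size is 14% − 6% = 8 points. Over this range of r the error is of similar order but stays below it.

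**Step 3: would the confidence interval show the problem?** With 1,000 women in the denominator (assumed), the 95% half-width at 14% is 1.96 × √(0.14 × 0.86 / 1,000) = 0.022, or 2.2 points. The number could well differ. With 5% to 50% of the 40,000 responding and 10% to 40% of responders in the transition (all assumed), the denominator runs from 40,000 × 0.05 × 0.10 = 200 to 40,000 × 0.50 × 0.40 = 8,000. The half-width then runs from 4.8 down to 0.8 points. Mailing more women shrinks the interval and leaves any selection error where it is.

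**Step 4: what could be said with no assumption about non-responders.** If 10% of women in the transition responded (assumed) and 14% of those scored 15 or more, the true prevalence in the mailed population could lie anywhere from 0.14 × 0.10 = 1.4% to 1.4% + 90% = 91.4%. At 50% response the bounds are 7% to 57%. These are logical limits and not plausible values. They show why the response rate belongs beside the estimate.

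**The case against.** The case for leaving aim 4 alone has real weight.

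- **The sampling is sound as far as it goes.** The 40,000 names are a random extraction from a compulsory roll. The respondents are self-selected members of a probability sample, not a convenience sample. That stands, but it does not bring in women outside Perth or make response independent of mood.
- **Every postal survey has non-response, and its handling may sit in an analysis plan not shown.** This also stands. The absence of weighting is no finding, and nothing in the article says that a crude proportion will be reported. The geographical mismatch differs, because it lies in the stated text and no analysis plan could repair it.
- **Aim 4 is a descriptive aim, listed last.** It bears on neither the randomisation nor the primary endpoint nor the treatment comparison. This is why the point is minor.

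Three stronger readings are tempting and should be resisted.

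- A reader might infer that prevalence is measured only in women who have consented to the trial. The article does not say what the returned form covers. It measures prevalence at screening, before the trial invitation, so responders with PHQ-9 ≥ 15 can be counted.
- A reader might infer from the exclusion "they receive medical treatment or undergo medical procedures that hinder ability to assign menopausal status" that women on hormonal treatment drop out of the prevalence estimate. That list governs entry to the trial. The article does not say how these women are handled in the prevalence denominator, and the screening questionnaire records hormone therapy and gynaecological surgery.
- A reader might infer that selection error would exceed the 8-point contrast. Over assumed ratios of 0.5 to 1.5 it reaches at most 6.5 points. A ratio of 2 would give 0.28 / 1.14 = 24.6%, an error of 10.6 points, but nothing in the document supports one ratio over another. The 14% and 6% also come from a cited survey and do not depend on aim 4.

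**Conclusion.** The point holds as a mismatch between the stated target population and the population the design can describe. The Perth restriction follows directly from the text and needs no assumption. The dependence on returned questionnaires is likewise stated, but its effect on the estimate is not known: neither direction nor size can be derived from the document. The range of 7.5% to 19.6% around a true 14% rests wholly on the assumed relative return rates of 0.5 to 1.5, and shows only that an error comparable to the 8-point contrast is possible. The consequence is confined to what may be concluded under aim 4. This is a minor point, worth correcting because the correction is nearly free.

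**What to change.** Restate aim 4 as the prevalence of PHQ-9 ≥ 15 among responding women aged 45 to 55 in metropolitan Perth whose menopausal transition status can be assigned. Report the estimate together with the response rate, and with a comparison of responders and the full roll extract on whatever data the extract holds.

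Weighting to such data would be optional. It could not correct response that depends on mood, nor recover women outside Perth.

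The cost is a reworded aim and one descriptive comparison, with no change to the mailing, eligibility or trial procedures. This matters because the article says recruitment is already under way. The small downside is a narrower claim.

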## Methods/Design

### Trial design

The Healthy Transition Trial (HTT) is a randomised, parallel, controlled trial of a telephone-driven health promotion intervention designed to prevent the onset of clinically significant symptoms of depression during the MT. The allocation ratio will be 1:1.

### Participants

We will use the Australian Electoral Commission roll to obtain a random extraction of 40,000 women aged 45 to 55 years living in the Perth metropolitan area (enrolment to vote is mandatory for all adults in Australia). They will be contacted by post to confirm their perimenopausal status (menopausal transition) and to assess the prevalence of clinically significant symptoms of depression (Patient Health Questionnaire, PHQ-9 score ≥15). They will be asked to return their screening questionnaire alongside the signed consent form, and those with PHQ-9 < 15 will be invited to join the trial. This screening questionnaire will take approximately 30 minutes to complete and will collect the following information:demographics including date and place of birth, age, marital status, number of children, educational attainment, living arrangements;regularity of menstrual cycles to establish menopausal status;history of life-limiting medical illnesses;presence of significant hearing or visual impairment;current and past common medical conditions, including depressive and anxiety disorders;alcohol use, as measured by the Alcohol Use Disorders Identification Test (AUDIT, details below);history of gynaecological surgery and medical procedures (for example, contraceptive implants) that may affect the assignment of menopausal status;prescription and non-prescription medications (including hormone therapy);depressive and anxiety symptoms, as rated by the Hospital Anxiety and Depression Scale (HADS, details below);past history of schizophrenia, schizoaffective, delusional or bipolar disorder; andgeneral practitioner’s (GP) details and permission for the study team to liaise with GP.

For the trial, we will include women who are:aged 45 to 55 years;experiencing no, or sub-threshold depressive symptoms (PHQ-9 < 15);experiencing recent (last 5 years) onset of irregular menstrual cycles (≥7 days difference in length of consecutive cycles) OR ≥2 skipped cycles and at least one interval of amenorrhea of 60 or more days; andamenorrhoeic for <12 months.

Volunteers will be excluded from participating for the following reasons:they disclose a history of gynaecological surgery that compromises the ability to assign menopausal status (that is, hysterectomy, bilateral oophorectomy, or endometrial ablation);they report an illness that may impact upon 12-month survival (for example, metastatic cancer);they receive medical treatment or undergo medical procedures that hinder ability to assign menopausal status (hormone therapy, hormonal intrauterine devices, contraceptive implants, patches or medications);there is evidence of clinically significant depressive symptoms (PHQ 9 ≥ 15) or major depressive episode at the time of assessment;there is evidence of concurrent alcohol abuse or dependency (AUDIT ≥15);they report past or current history of schizophrenia, delusional, schizoaffective or bipolar disorder;there is evidence of significant hearing impairment that may compromise telephone communication;they are not fluent in written or spoken English;they plan to leave Western Australia within the following 12 months;they report active suicidal ideation;they do not have an active GP or do not consent to the research team liaising with their GP throughout the course of the study; orthey fail to provide written informed consent.

